#### **7.3.4.1 Solicited symptoms**

Information of solicited symptoms/AEs will be collected by the subjects in the provided diary cards during a 7-day follow-up period after each vaccination (i.e. day of vaccination and 6 subsequent days), and reported by the investigator team.

A solicited local and general symptoms or AEs are the one whose nature or intensity is consistent with the expected AEs described and listed in [Table 7-1](#).

**Table 7-1 Solicited local and general symptoms /adverse events:**

| Solicited local (at injection site) AEs                                                                                                                                                                                                                   | Solicited general AEs                                                                                                                                                                                                                   |
|-----------------------------------------------------------------------------------------------------------------------------------------------------------------------------------------------------------------------------------------------------------|-----------------------------------------------------------------------------------------------------------------------------------------------------------------------------------------------------------------------------------------|
| 
 
○ Pain at the injection site
 
○ Tenderness at the injection site
 
○ Redness at the injection site
 
○ Swelling at the injection site
 
○ Ecchymosis at the injection site
 
 | 
 
○ Fever*
 
○ Nausea/Vomiting
 
○ Diarrhea
 
○ Appetite loss
 
○ Headache
 
○ Myalgia
 
○ Joint pain
 
○ Fatigue
 
○ Shivering
 
 |

---

\* Oral temperature will be recorded in the evening. Should additional temperature measurements be performed at other times of day, the highest temperature will be recorded.

The oral temperature will be monitored every evening until 6 days after each vaccination. If it has been measured for more than one time, only the highest level should be recorded in the diary card. Subjects with an oral temperature  $\geq 37.5^{\circ}\text{C}$  will be defined as fever.

#### 7.3.4.2 Unsolicited symptoms

An unsolicited local and general AE or symptoms are the one whose nature or intensity is NOT consistent with the expected AEs described and listed above in this protocol. Information of unsolicited symptoms/AEs will be collected during a 21-day follow-up period after each vaccination (i.e. day of vaccination and 20 subsequent days) and reported at each visit.

#### 7.3.5. Adverse events (AEs)

An adverse event (AE) is defined as any untoward medical occurrence in a subject or clinical investigation subject administered a pharmaceutical product and which does not necessarily have to have a causal relationship with this treatment. An AE can therefore be any unfavorable and unintended sign, symptom, or disease temporally associated with the use of a medicinal product, whether or not considered related to the medicinal product. However, abnormal laboratory values or changes are not automatically reported as adverse events if they are not clinically significant. They will only be recorded as adverse events if a therapeutic action needed or judged by the investigators.

The occurrence of adverse events should be sought by non-directive questioning of the subject at each visit and telephone follow-up (i.e. 7-day/14-day post-vaccination follow-up, and last 2 telephone visits, Visit 6 and Visit 7) during the study. Adverse events also may be detected when they are volunteered by the subject during or between visits or through physical examination, laboratory test or other assessments. All adverse events must be recorded on the Adverse Events CRF with the following information:

1. AE term and description
2. its duration (onset and resolution dates or if continuing at final exam)
3. the severity grade (mild, moderate, severe)
4. whether it constitutes a serious adverse event (SAE)

5. its relationship to the study vaccine (certain/probably-likely/possible/unlikely/unrelated)
6. action taken treatment required
7. outcome (resolved/not resolve/resolved with residual effect/other)

#### **7.3.5.1 The severity grade of AE and solicited/unsolicited symptoms**

The severity of solicited and unsolicited symptoms will be assessed as [Table 7-2](#). It should be scored by subject self if any symptom occurs.

In the diary card, redness / swelling / hematoma at injection site will be recorded as greatest surface diameter in mm, and the maximum oral temperature will be recorded in °C.

**Table 7-2 Intensity scales of solicited/unsolicited symptoms:**

| Adverse Event                                                                   | Severity grade | Parameter                                                     |
|---------------------------------------------------------------------------------|----------------|---------------------------------------------------------------|
| Solicited local AEs                                               |                |                                                               |
| Pain at injection site                                                          | 0              | Absent                                                        |
|                                                                                 | 1              | On touch                                                      |
|                                                                                 | 2              | When limb is moved                                            |
|                                                                                 | 3              | Prevents normal activity                                      |
| Injection site:
Tenderness / Redness /
Swelling / Ecchymosis*             | 0              | 0 mm                                                          |
|                                                                                 | 1              | > 0 to ≤ 20 mm                                                |
|                                                                                 | 2              | > 20 to ≤ 50 mm                                               |
|                                                                                 | 3              | > 50 mm                                                       |
| Solicited general AEs                                             |                |                                                               |
| Fever**                                                                         | 0              | < 37.5°C                                                      |
|                                                                                 | 1              | ≥ 37.5 to ≤ 38.0°C                                            |
|                                                                                 | 2              | > 38.0 to ≤ 39.0°C                                            |
|                                                                                 | 3              | > 39.0 °C                                                     |
| Nausea/Vomiting                                                                 | 0              | Normal                                                        |
|                                                                                 | 1              | Easily tolerated or
1-2 episodes/day                       |
|                                                                                 | 2              | Interferes with normal activity or
> 2 episodes/day        |
|                                                                                 | 3              | Prevents normal activity,
requires outpatient IV hydration |
| Diarrhea                                                                        | 0              | Normal                                                        |
|                                                                                 | 1              | 2-3 loose stools/day                                          |
|                                                                                 | 2              | 4-5 stools/day                                                |
|                                                                                 | 3              | > 6 watery stools/day or
requires outpatient IV hydration  |
| Appetite loss / Headache /
Myalgia / Joint pain
Fatigue / Shivering       | 0              | Normal                                                        |
|                                                                                 | 1              | Easily tolerated                                              |
|                                                                                 | 2              | Interferes with normal activity                               |
|                                                                                 | 3              | Prevents normal activity                                      |
| Unsolicited AEs                                                   |                |                                                               |
| Unsolicited symptom(s)                                                          | 0              | Normal                                                        |
|                                                                                 | 1              | Easily tolerated                                              |
|                                                                                 | 2              | Interferes with normal activity                               |
|                                                                                 | 3              | Prevents normal activity                                      |
| * Record greatest surface diameter in mm.                                       |                |                                                               |
| # Record oral temperature in °C. Fever is defined as oral temperature ≥ 37.5°C. |                |                                                               |

The investigator will make an assessment of the maximum intensity that occurred over the

duration of the event for all other AEs reported during the study period. The assessment will be based on the investigator's clinical judgment. The severity of each AE and SAE recorded in the CRF should be assigned to one of the categories described in [Table 7-3](#).

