## 9. Study Endpoints

### 9.1. Primary endpoint

- ◆ The percentage, intensity and relationship to vaccination of local and systemic signs and symptoms at a 5- $\mu$ g and 10- $\mu$ g dose under the following time frames:
  - Solicited adverse events: during 7-day follow-up period
  - Unsolicited adverse events: during 21-day follow-up period
- ◆ The occurrence of overall adverse events and serious adverse event at a 5- $\mu$ g and 10- $\mu$ g dose during the entire study period.

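### Table 7-2 cannot validly grade tenderness or exactly 6 stools a day, and the solicited and unsolicited definitions overlap, so part of the primary endpoint's intensity data is undefined or inconsistently assignable

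*Protocol*

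**What the plan says.** Section 9.1 makes intensity part of the primary endpoint: "The percentage, intensity and relationship to vaccination of local and systemic signs and symptoms". Section 7.3.5.1 has subjects score solicited and unsolicited symptoms themselves, using Table 7-2.

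- **Tenderness.** Table 7-1 lists "Tenderness at the injection site" as a solicited local event in its own right, separate from pain. Table 7-2 puts it in the row beginning "Tenderness / Redness", with bands 0, >0 to 20, >20 to 50 and >50 mm. The row's footnote reads "Record greatest surface diameter in mm". Section 7.3.5.1, on what the diary captures, says that "redness / swelling / hematoma at injection site will be recorded as greatest surface diameter in mm"; tenderness is not in that list.
- **Diarrhoea.** Grade 1 is "2-3 loose stools/day", grade 2 is 4-5 stools a day, and grade 3 is "> 6 watery stools/day" or a need for outpatient IV hydration.
- **Solicited or unsolicited.** Section 7.3.4.1 calls an event solicited if its nature or intensity is consistent with the events in Table 7-1. Section 7.3.4.2 calls it unsolicited if it is one "whose nature or intensity is NOT consistent with the expected AEs". Table 7-1 lists terms only, with no intensities. Collection runs for 7 days after each vaccination for solicited events and 21 days for unsolicited ones.

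**The concern.** A scale that subjects apply at home has to be usable as printed. A subject whose arm is tender but unmarked has nothing visible to measure. That subject might enter 0 mm (grade 0), estimate the tender area, or report the symptom only under pain, whose grade 1 is already pain on touch. A subject with 6 stools in a day has no grade to choose. A site holding a listed symptom of surprising severity finds two definitions that both apply.

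These are faults in data capture. The analysis cannot recover a grade that the diary never recorded validly. The grades feed the severity summary, which Section 10.3.2 presents with the counts, percentages and 95% confidence intervals for each dose and overall.

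**Working it through.** The plan states no figure to reproduce here: Section 10.6 marks sample size as not applicable, and Section 10.3.2 plans no hypothesis for the primary endpoint. The check is of the scale's logic, plus the size of one misgraded subject.

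**1. Does each value get exactly one grade in Table 7-2?**

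| Stools per day | Grade |
|---|---|
| 0-1 | no numeric band; can be read as grade 0 |
| 2-3 | 1 |
| 4-5 | 2 |
| 6 | none, unless IV hydration is needed |
| 7 or more | 3 |

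The description also shifts between grades, from loose stools to stools to watery stools. The same test on the mm bands (0 to 99.9 mm) and the fever bands (35.0 to 41.9 °C), in steps of 0.1, found no gap and no overlap. The numeric gap is confined to diarrhoea.

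**2. Tenderness: table against diary text.** Table 7-2 needs a diameter for four reactions: tenderness, redness, swelling and ecchymosis. Section 7.3.5.1 provides one for three: redness, swelling and hematoma. Taking hematoma and ecchymosis as the same item, tenderness is the one left without a stated measurement. It is 1 of the 5 solicited local terms. The footnote mark sits at the end of the row label, but even if it belonged to ecchymosis alone, the only bands offered for tenderness are in mm.

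**3. Solicited and unsolicited: truth table of the two definitions.** Solicited = nature fits OR intensity fits. Unsolicited = nature does not fit OR intensity does not fit.

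| Nature fits | Intensity fits | Solicited (7.3.4.1) | Unsolicited (7.3.4.2) |
|---|---|---|---|
| yes | yes | yes | no |
| yes | no | yes | yes |
| no | yes | yes | yes |
| no | no | no | yes |

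Two of the four cases meet both definitions. Because Table 7-1 states no expected intensity, the second column cannot be filled in from the protocol.

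**4. Does the choice change anything?** Under the solicited rows of Table 7-2, redness above 50 mm, or a temperature above 39.0 °C, is grade 3 on measurement alone. The unsolicited row grades by effect on activity, so the same event, if well tolerated, is grade 1. The collection window also changes, from 7 to 21 days.

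**5. Size of one misgraded subject.** From Table 6-1, A05 = 1 + 1 + 3 + 25 = 30 and B10 = 1 + 4 + 25 = 30. One subject moved into or out of a grade shifts that arm's rate by 1/30 = 3.3 percentage points. With exact (Clopper-Pearson) 95% intervals:

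- 0/30 = 0% (0 to 11.6%)
- 1/30 = 3.3% (0.1 to 17.2%)
- 2/30 = 6.7% (0.8 to 22.1%)

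**The case against.** A reader might infer that the protocol moves the severest solicited reactions into the unsolicited category and so biases grade 3 rates downwards. The documents do not support that. Section 7.3.4.2 read alone could suggest it, but under Section 7.3.4.1 a listed symptom still qualifies as solicited by its nature. Table 7-2 also places open-ended top grades under its solicited headings, which suggests that any intensity of a listed symptom was meant to stay there. An event filed as unsolicited would still carry a 0-3 grade, and Section 10.3.2 tabulates both kinds. What remains is an overlap that can alter the scale and the window, as step 4 shows.

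A reader might also count all 60 × 2 = 120 post-vaccination diaries as affected. That is exposure to the flaw. Only diaries from subjects with tenderness could be misgraded, and the protocol gives no expected rate.

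Other points on the plan's side:

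- Each adverse event in the CRF also gets an investigator severity category from Table 7-3, which is functional. This is a partial backstop, but it does not repair the Table 7-2 grade.
- Pain grade 1 already covers pain on touch, so some tenderness will be captured there. That stands, and it means a new tenderness scale must not simply duplicate the pain item.
- The mm row may be a grouping slip, and the diary card itself is not in the protocol. That is possible, but the table and Section 7.3.5.1 still disagree as written.
- The primary analysis is descriptive, so no decision threshold is crossed. This limits the consequence but does not make the grades valid.

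**Conclusion.** The point holds in three parts. Tenderness, 1 of 5 solicited local terms, is graded by a diameter that the diary text does not provide for. Exactly 6 stools a day without IV hydration has no grade. The solicited and unsolicited definitions overlap on an expected intensity that is never stated. Followed as written, the affected grades and categories are undefined or can be assigned differently by different subjects and sites.

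The direction of error is not fixed. Unmarked tenderness entered as 0 mm would be understated, but other entries are equally open, and 6 stools could be left blank or graded either way.

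The 3.3 points is the effect of one misgraded subject. It rests on 30 evaluable subjects per dose and is not an estimate of how often misgrading will occur. The matter should be corrected before data collection, since analysis cannot restore what was not captured.

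**What to change.** Before the diary card is printed:

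1. Take tenderness off the mm row of Table 7-2. Either grade it on a functional scale that is distinct from the pain item, or merge it with pain. Bring Section 7.3.5.1 and Table 7-2 into line on which reactions are measured in mm, and use one term for ecchymosis or hematoma.
2. Make the diarrhoea bands contiguous so that every stool count has exactly one grade, and use the same stool description across grades. Where the boundary falls is for the clinical team.
3. Define solicited by listed term and 7-day window only, and delete the words *or intensity* from Sections 7.3.4.1 and 7.3.4.2.

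The cost is edits to Table 7-2, Sections 7.3.4.1, 7.3.4.2 and 7.3.5.1, and the diary card (also Table 7-1 if tenderness is merged with pain). No visit, test or procedure is added.

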**Table 7-3 Intensity scales of AE:**

| Severity of AE | Description                                                                                                                                                                                                                                          |
|----------------|------------------------------------------------------------------------------------------------------------------------------------------------------------------------------------------------------------------------------------------------------|
| 1. Mild        | Signs or symptoms are being aware of but can be tolerated easily. Signs or symptoms are of minor irritant type and are transient. Symptoms would not require medication or a medical evaluation and there is no loss of time from normal activities. |
| 2. Moderate    | Signs or symptoms cause enough discomfort to interfere with usual activities.                                                                                                                                                                        |
| 3. Severe      | Signs or symptoms are incapacitating; subject is unable to do work or usual activities. Signs or symptoms may be of systemic nature or require medical evaluation and/or treatment.                                                                  |

#### 7.3.5.2 The relationship to study vaccine

**Table 7-4 The relationship between AE and study vaccine:**

| Relationship    | Description                                                                                                                                                                                                                                                                                                                                                                                                                      |
|-----------------|----------------------------------------------------------------------------------------------------------------------------------------------------------------------------------------------------------------------------------------------------------------------------------------------------------------------------------------------------------------------------------------------------------------------------------|
| Certain         | A clinical event, including laboratory test abnormality, occurring in a plausible time relationship to drug administration, and which cannot be explained by concurrent disease or other drugs or chemicals. The response to withdrawal of the drug (dechallenge) should be clinically plausible. The event must be definitive pharmacologically or phenomenologically, using a satisfactory rechallenge procedure if necessary. |
| Probably/likely | A clinical event, including laboratory test abnormality, with a reasonable time sequence to administration of the drug, unlikely to be attributed to concurrent disease or other drugs or chemicals, and which follows a clinically reasonable response on withdrawal (dechallenge). Rechallenge information is not required to fulfill this definition.                                                                         |
| Possible        | A clinical event, including laboratory test abnormality, with a reasonable time sequence to administration of the drug, but which could also be explained by concurrent disease or other drugs or chemicals. Information on drug withdrawal may be lacking or unclear.                                                                                                                                                           |
| Unlikely        | A clinical event, including laboratory test abnormality, with a temporal relationship to drug administration which makes a causal relationship improbable, and in which other drugs, chemicals or underlying disease provide plausible explanations.                                                                                                                                                                             |
| Unrelated       | A clinical event, including laboratory test abnormality, which is clearly not related to drug administration.                                                                                                                                                                                                                                                                                                                    |

The investigator will make an assessment of the relationship between investigational vaccine and the occurrence of each AE/SAE, including all solicited/unsolicited reactions to

vaccination. The reasonable possibility will be determined based on the investigator's clinical judgment. The causality should be considered as one of the categories described in [Table 7-4](#).

The adverse events should be followed till Day 210 for safety assessments. Each event should be followed until resolution or the event is considered stable. Both regular return and telephone contact will be acceptable.

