### 8.4. Study stopping criteria

Throughout the study period, if any SAE or serious complain happens, PI is obligated to review subject's data immediately and make medical judgment if the SAE is vaccine-related or not. If any of the following situations occurs, PI must inform the DSMB and NHRI/CRO and study recruitment should be suspended until further notice.

- (1) Any subject with severe local reaction, including ulceration, abscess or necrosis.
- (2) Any subject develops laryngospasm, bronchospasm or anaphylaxis.
- (3) Two of more subjects develop severe urticaria.
- (4) Any vaccine-related SAE during study period.

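### Table 7-4 grades causality by response to drug withdrawal, which an injected vaccine dose cannot show, so a clear vaccine reaction has no category that fits

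*Protocol*

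**What the plan says.** Section 7.3.5 lists relationship to the study vaccine among the items recorded on the Adverse Events CRF, on five levels. Section 7.3.5.2 and Table 7-4 define those levels:

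- *Certain*: plausible timing and no other explanation. On withdrawal: "The response to withdrawal of the drug (dechallenge) should be clinically plausible". On rechallenge: "using a satisfactory rechallenge procedure if necessary".
- *Probably/likely*: reasonable timing, another cause unlikely, and an event "which follows a clinically reasonable response on withdrawal (dechallenge". Rechallenge information is expressly waived.
- *Possible*: reasonable timing, "but which could also be explained by concurrent disease or other drugs or chemicals". Here alone the table relaxes the withdrawal element: "Information on drug withdrawal may be lacking or unclear".
- *Unlikely* and *Unrelated*: timing and other causes speak against the vaccine, or the event is clearly not related.

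The text after the table applies these levels to every AE and SAE, including all solicited and unsolicited reactions, and adds: "The reasonable possibility will be determined based on the investigator's clinical judgment".

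The grade feeds the primary endpoint in section 9.1: "The percentage, intensity and relationship to vaccination of local and systemic signs and symptoms". Section 10.3.2 says that relationship will be summarised descriptively, with no hypothesis. The regimen is two intramuscular injections, on Day 0 and Day 21.

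**The concern.** The scale relies on an observation that this product does not offer. With a daily drug, the clinician stops it and sees whether the event subsides. With an injected inactivated-virus vaccine, the exposure has been delivered in full before any reaction appears. A criterion that cannot be observed sits in both upper levels of the scale, and the protocol does not say how to read it for a vaccine.

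Two careful raters can therefore grade the same event differently. One takes the withdrawal clause at face value and moves a clear reaction down to *Possible*. The other ignores the clause, or counts spontaneous resolution as satisfying it, and grades *Certain* or *Probably/likely*. Part II runs in two centres, so such a difference could become a centre difference. The trial is open-label and uncontrolled, so there is no placebo rate to fall back on for attribution, and the investigator's causality grade carries that weight.

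**Working it through.** No arithmetic decides this point. The check is to take one ordinary event through each definition: injection-site pain within hours of a dose, in a healthy volunteer with no other illness or drug that could explain it.

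| Level | What Table 7-4 asks for | Does the test event fit? |
|---|---|---|
| *Certain* | Plausible timing; no other explanation; plausible response to withdrawal; rechallenge only if needed | Timing and absence of another cause are met; there is no withdrawal to observe |
| *Probably/likely* | Reasonable timing; other cause unlikely; reasonable response on withdrawal | Same gap; the withdrawal element is part of the definition and is not waived |
| *Possible* | Reasonable timing; another explanation available; withdrawal information may be missing | No: there is no other explanation |
| *Unlikely* | Timing that makes causality improbable; other plausible causes | No on both counts |
| *Unrelated* | Clearly not related | No |

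The test event fits no level as written, yet section 7.3.5.2 requires it to be placed in one.

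**Can the second dose stand in for withdrawal?** Section 4.3.2 allows further vaccination to be discontinued. That withholds a future exposure; it does not remove the dose already given. With 60 subjects and two doses there are at most 60 × 2 = 120 subject-dose periods. The 60 that follow the second dose have no further dose to withhold. Recurrence after the second dose is informative for events seen after the first, but it is rechallenge evidence, not dechallenge evidence.

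**Is the silence on vaccines a waiver?** The table states its exceptions where it intends them: rechallenge information is not needed for *Probably/likely*, and withdrawal information may be absent for *Possible*. No such exception covers withdrawal under *Probably/likely*. The wording under *Certain* is if anything softer, so the highest level could be easier to reach than the one below it.

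**What depends on the grade?**

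- Counts, percentages and 95% confidence intervals for AEs (section 10.3.2): no.
- Intensity (Tables 7-2 and 7-3): no.
- Overall AE and SAE occurrence (section 9.1): no.
- The relationship component of the primary endpoint: yes.

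The primary analysis is descriptive and section 10.6 gives no power calculation, so no error rate, power or sample size changes.

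**The case against.** The best reply is that the scale is a guide to judgment, not a checklist. *Certain* uses *should* and asks for rechallenge only where necessary. The text after the table leaves the decision to clinical judgment. Events are followed to resolution or stability, so a rater may treat a transient reaction that subsides as a plausible course after exposure ended. Many systemic symptoms, such as headache or fatigue, often have another possible cause and then fit *Possible* without strain.

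Much of this stands. A reader might infer that no event can ever be rated *Certain* or *Probably/likely*, so that the rate of related events at those levels must be 0%. The documents do not support that: the softer wording and the appeal to judgment leave the upper levels reachable. A reader might also infer that the endpoint is in fact misgraded. Nothing in the protocol shows this; it shows only that grading is exposed to differing readings. The difficulty is concentrated in clear reactions with no alternative cause, not in every event.

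The reply does not close the gap. Counting natural resolution as dechallenge empties the clause, because nothing was withdrawn. It also takes time, whereas sections 3.1 and 8.4 call for an immediate judgment on relatedness. Judgment exercised against an inapplicable criterion is where raters part company.

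A further inference is that the suspension rule fails for the same reason. Section 8.4 lists "Any vaccine-related SAE during study period", but asks the investigator for a direct related-or-not judgment and does not cite Table 7-4; its other three criteria need no causality grade. The missing link between the five levels and the term used there is a separate, smaller wording gap. A related/unrelated cut for summary tables is commonly left to the SAP and is not criticised here.

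**Conclusion.** The point holds as a defect of wording with a limited reach. Table 7-4 contains a withdrawal condition that an injected dose cannot meet and, read literally, leaves a clear vaccine reaction without a fitting level. The relationship component of the primary endpoint is therefore open to inconsistent grading between raters and centres, or to down-grading to *Possible*. The size of the effect cannot be computed from the protocol, because it depends on how each rater resolves the ambiguity.

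This rests on two assumptions: that raters give the table's definitions some literal weight, and that no vaccine-specific guidance on dechallenge exists outside the protocol, such as CRF completion instructions. If such guidance exists, the remedy reduces to bringing it into the protocol.

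**What to change.** In Table 7-4, remove the dechallenge condition from *Certain* and *Probably/likely*, and the withdrawal sentence from *Possible*. Define the levels by plausible time from injection, presence or absence of another likely cause, and recurrence after the second dose where applicable. Leave each assessment to the investigator; there is no need to declare local reactions related in advance.

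Separately, the five-level scale and the term *vaccine-related* in sections 8.3.2 and 8.4 should be reconciled. Which levels count for that purpose is for the sponsor and the DSMB to decide.

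The cost is a wording change in one table, a sentence linking it to sections 8.3.2 and 8.4, and an update to the CRF guidance. No visit, procedure or subject is added. The small downside is that more events may be graded in the upper levels.
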